### Biological data acquisition

2.6

Biological data will be collected at three time points: baseline, trial completion (week 12), and 12-week follow-up (week 24). MRI scans will be acquired using a 3.0T Siemens Skyra scanner (Erlangen, Germany) at Zigong Mental Health Center. The data to be analyzed will include gray matter volume, cortical thickness, amplitude of low-frequency fluctuations (ALFF), bilateral hippocampal connectivity, posterior cingulate cortex (PCC) functional connectivity, default mode network (DMN) connectivity, and frontal network connectivity. Additionally, blood samples will undergo metabolomic analysis using mass spectrometry, while fecal samples will be analyzed for microbiome changes via 16S rRNA gene sequencing. All laboratory procedures will follow standardized protocols.

### Procedure

2.7

Participants are being recruited through community health center flyers and digital advertisemts onen WeChat platform. Interested individuals attend screening visits at local community health centers where they complete standardized assessments including the AD8, ISI, PHQ-9, GAD-7, MMSE, and MoCA scales. Potentially eligible individuals will undergo face-to-face diagnostic evaluations conducted by senior psychiatrists from the Zigong Mental Health Center. Participants diagnosed with MCI who meet inclusion and exclusion criteria undergo informed consent procedures followed by comprehensive baseline assessments within 1 week, including collection of demographic data, 3-day food diary, functional assessments (ADL and IADL), symptom and quality-of-life measures (GSRS and WHOQOL-OLD), and biological data (blood samples, fecal samples, cranial MRI). Participants are then randomly allocated to either the intervention group or the waitlist group. The intervention group will receive a combination of PE, TCT, and VRCT, while the control group will not receive any intervention during the study period. To compensate, the waitlist control group will be offered the same training after the follow-up assessment. The CONSORT diagram depicting participant flow is presented in Figure 1, and the time points for data collection are detailed in Table 3.

**FIGURE 1 F1:**
[figure not shown]
Consolidated Standards of Reporting Trials (CONSORT) diagram.

**TABLE 3 T3:** Outline of study assessments and timelines.

Items	Screening	Week 0 (baseline)	Week 6 (mid-intervention)	Week12 (post-intervention)	Week 24 (12-week follow-up)
Informed consent	–	×	–	–	–
Randomization	–	×	–	–	–
Demographic information	–	×	–	–	–
Food diary	–	×	–	×	×
AD8	×	–	×	×	×
ISI	×	–	×	×	×
PHQ9	×	–	×	×	×
GAD7	×	–	×	×	×
AVLT	–	×	×	×	×
TMT (A and B)	–	×	×	×	×
DST (forward and backward)	–	×	×	×	×
MMSE	×	–	×	×	×
MOCA	×	–	×	×	×
ADL	–	×	×	×	×
IADL	–	×	×	×	×
GSRS	–	×	×	×	×
WHOQOL-OLD	–	×	×	×	×
Blood sample collection	–	×	–	×	×
Fecal sample collection	–	×	–	×	×
Magnetic resonance imaging (MRI)	–	×	–	×	×

AD8, Alzheimer’s Disease 8-item scale; ISI, Insomnia Severity Index; PHQ-9, Patient Health Questionnaire-9; GAD-7, Generalized Anxiety Disorder 7-item scale; MMSE, Mini-Mental State Examination; MOCA, Montreal Cognitive Assessment; ADL, Activities of Daily Living scale; IADLs, Instrumental Activities of Daily Living scale; GSRS, Gastrointestinal Symptom Rating Scale; WHOQOL-OLD, World Health Organization Quality of Life Instrument–Older Adults Module; AVLT, Chinese Auditory Verbal Learning Test; TMT (A and B), Trail Making Test (Parts A and B); DST, Digit Span Test (forward and backward).

### Statistical analysis

2.8

#### Sample size

2.8.1

Sample size estimation was performed using G*Power 3.1.9.7 based on the primary outcome of change in the memory-weighted cognitive composite score. Assuming a moderate effect size (f = 0.25), α = 0.05, and 90% power for a repeated-measures ANOVA, the minimum required sample size is 46 participants. To account for a 30% dropout rate, we will enroll 66 participants.

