### Study design

2.1

This single-blind, randomized controlled trial (ChiCTR2400093397, www.chictr.org.cn) employs a two-arm parallel design, consisting of an intervention group receiving a combination of VRCT, TCT, and PE, and a waitlist control group who will receive no training during the research period. As compensation, the waitlist group will be offered the same training after the follow-up assessment. All participants will undergo comprehensive assessments at four time points: baseline (week 0), mid-intervention (week 6), post-intervention (week 12), and a 12-week follow-up (week 24). The trial is designed in accordance with the CONSORT (Consolidated Standards of Reporting Trials) guidelines and will be conducted and reported accordingly.

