#### Statistical considerations

2.8.2

The analysis will adhere to the eHealth Consolidated Standards of Reporting Trials (CONSORT) criteria (Eysenbach, 2011), follow the intention-to-treat principle and per protocol set. The per-protocol set included participants who attended at least 70% of the assigned intervention sessions and completed all protocol-specified assessments (Zhang et al., 2018). Statistical analyses will be conducted using IBM SPSS Statistics (Version 24.0; IBM Corp., Armonk, NY, United States). Continuous variables are presented as mean and standard deviation; categorical variables as frequency and percentages.

For baseline characteristics, continuous variables are compared between groups using *t*-test, while categorical variables are analyzed using chi-square test. Primary outcomes will be analyzed using two-way repeated-measures ANOVA, evaluating the main effects of group, time, and their interaction. *Post-hoc* pairwise comparisons were conducted with Bonferroni correction for multiple comparisons. Missing follow-up data will be imputed using the last observation carried forward (LOCF) method. Sensitivity analyses (completers-only and per-protocol) will assess potential bias due to dropouts and imputation methods. We will also compare baseline characteristics between participants who dropped out and those who completed the study. All tests are two-sided, with statistical significance defined as *p* < 0.05.

Multimodal neurobiological correlates of treatment response will be assessed by integrating structural/functional MRI, gut microbiome, and plasma metabolome with behavioral outcomes. For analyses involving gut microbiota, key dietary patterns extracted from the 3-day food diaries will be included as covariates to enhance the validity of the findings. Hypothesis-driven analyses will include: (i) partial least squares (PLS) regression to identify multivariate brain-behavior associations, (ii) mixed-effects modeling for longitudinal effects, and (iii) mediation analysis to test whether brain-gut axis changes drive clinical improvement. Significance thresholds will be adjusted via Holm-Bonferroni correction.

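### Section 2.8.1 claims 90% power for a moderate effect, but an interaction f of 0.25 means a between-arm difference in change of at least 1.0 SD, which is large

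*Protocol article*

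**What the plan says.** The protocol article, section 2.8.1 (Sample size), names its software and target: "Sample size estimation was performed using G*Power 3.1.9.7 based on the primary outcome of change in the memory-weighted cognitive composite score". Its inputs are: "Assuming a moderate effect size (f = 0.25), α = 0.05, and 90% power for a repeated-measures ANOVA". The result is that "the minimum required sample size is 46 participants", followed by "To account for a 30% dropout rate, we will enroll 66 participants". The paragraph does not say which ANOVA effect was powered, how many measurements were entered, or what correlation and epsilon were used. It gives no difference on the composite scale.

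Section 2.1 (Study design) states: "All participants will undergo comprehensive assessments at four time points". These are weeks 0, 6, 12 and 24, and Table 3 places the component tests of the composite at all four. Section 2.8.2 (Statistical considerations) states: "Primary outcomes will be analyzed using two-way repeated-measures ANOVA", with group, time and their interaction as the effects.

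Section 2.5 says the composite was built to pick up small changes during the trial. The limitations in section 3 give greater sensitivity to such changes as the reason it replaced the MoCA as primary outcome.

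**The concern.** An f of 0.25 carries the conventional label of a medium effect, and readers tend to equate that with half a standard deviation between two groups. That equation holds for a comparison of two means. It does not hold for a group-by-time interaction, where the same f corresponds to a difference in change at least twice as large.

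If the label is taken at face value, the trial appears to have 90% power for a moderate cognitive benefit. A non-significant result could then be read as evidence against such a benefit, when the design would probably have missed it. The label also conflicts with the stated reason for choosing the composite.

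**Working it through.** **Inputs from the article:** f = 0.25, alpha = 0.05, power 90%, total N = 46, dropout 30%, enrolled N = 66, two arms at 1:1, four visits. **Assumed, because not stated:** interaction test, rho = 0.5, epsilon = 1 (G*Power defaults), then varied.

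**1. Reproducing 46 and 66.** For the interaction with two groups and m measurements, the noncentrality is λ = f²·N·m·ε/(1 − ρ), with df1 = (m − 1)ε and df2 = (N − 2)(m − 1)ε.
- m = 2, N = 46: λ = 0.0625 × 46 × 2 / 0.5 = 11.5, df 1 and 44, power 91.2%.
- m = 2, N = 44: λ = 11.0, power 89.97%, just short. So 46 is the answer.
- At the same settings m = 3 gives 36 and m = 4 gives 30.
- With m = 4 and N = 46: λ = 0.0625 × 46 × 4 / 0.5 = 23, power 98.6%.
- Four visits also return 46 with rho about 0.22–0.24 (epsilon 1), or with rho 0.5 and epsilon about 0.55.
- G*Power's other two effect-size conventions do not give 46 at rho = 0.5, epsilon = 1: 174, 106 and 80 (SPSS option) or 172, 104 and 78 (Cohen option) for 2, 3 and 4 measurements.
- Dropout: 46/0.7 = 65.7, rounded up to 66. Correct.

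**2. What f = 0.25 means.** Let d_j be the between-arm difference at visit j. With equal arms the interaction cell effects are ±(d_j − d̄)/2, so f = ½ × SD(d_j)/σ, where the SD is taken over visits with divisor m and σ is the outcome SD. An SD cannot exceed half the range, so f ≤ range/(4σ), and range ≥ 4 × 0.25σ = 1.0σ. The range is the largest between-arm difference in change between any two visits. Neither rho nor epsilon enters.

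For particular patterns (difference at weeks 0, 6, 12, 24 as a fraction of its peak δ):
- Two visits (0, 1): f = δ/4σ, so δ = 1.0 SD.
- Sustained (0, 1, 1, 1): f = 0.2165 δ/σ, so δ = 1.15 SD.
- Build and hold (0, ½, 1, 1): f = 0.2073 δ/σ, so δ = 1.21 SD.
- Build and fade (0, ½, 1, ½): f = 0.1768 δ/σ, so δ = 1.41 SD.

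**3. Power for δ = 0.5 SD** (my benchmark for moderate).

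| Test and pattern | rho | N = 46 | N = 66 |
|---|---|---|---|
| Two visits, f = 0.125 | 0.3 | 29% | 39% |
| Two visits | 0.5 | 38% | 52% |
| Two visits | 0.7 | 57% | 73% |
| Four visits, sustained, f = 0.108 | 0.3 | 27% | 39% |
| Four visits, sustained | 0.5 | 37% | 52% |
| Four visits, sustained | 0.7 | 59% | 77% |
| Four visits, build and hold, f = 0.104 | 0.5 | 35% | 48% |
| Four visits, build and fade, f = 0.088 | 0.5 | 26% | 36% |

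Example, sustained at rho = 0.5: f² = (0.5 × 0.2165)² = 0.01172. With N = 46, λ = 0.01172 × 46 × 4 / 0.5 = 4.31 on 3 and 132 df. With N = 66, λ = 6.19 on 3 and 192 df.

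**4. Difference with 90% power.** Solving the same formula for the sustained four-visit pattern at rho = 0.5 gives 0.92 SD with 46 and 0.77 SD with 66 (0.764, rounded up).

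**The case against.** Several points count against a harsher reading.

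- **A reader might infer that 46 can come only from a two-visit calculation, and so is an arithmetic error.** The article does not support that. It states neither rho nor epsilon, and four visits with a lower value of either also give 46. Both 46 and 66 are arithmetically sound.
- **A reader might infer that the mismatch with four visits leaves the trial too small for its stated f.** The reverse is true at default settings: four visits need 30, and 46 gives 98.6% power.
- **One reading does make f = 0.25 equal to 0.5 SD.** For the group main effect f = δ/(2σ), and with four visits and rho = 0 that test also needs 46. But it requires zero correlation between repeated tests on the same person (at rho = 0.5 it needs 108). It also averages in the baseline, where randomised arms should not differ, and it does not test change, which section 2.8.1 says was the basis.
- **The article never claims power for 0.5 SD.** True: the word moderate is attached to an f value, and 0.5 SD is my benchmark. The power figures depend on rho and on the shape of the effect over time, so they are a range. The 1.0 SD lower bound does not depend on them.
- **The unstated software settings** may be in the full protocol or analysis plan, and I do not count their absence as a fault. The point rests on what the paragraph does state.

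**Conclusion.** The point stands as a misdescribed effect size. Under the interaction reading that matches a sample size based on change, f = 0.25 assumes a between-arm difference in change of at least 1.0 outcome SD: 1.15 SD if sustained, and about 1.2 to 1.4 SD if gradual or fading. That bound needs only two equal arms and the default definition of f. It is a large effect, so section 2.8.1 does not establish 90% power for a moderate one.

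For 0.5 SD at rho = 0.5, power is about 37–38% with 46 analysed and 52% with 66, taking the two-visit and sustained four-visit cases. Over rho from 0.3 to 0.7 the two-visit figures run from 29% to 57% with 46 and from 39% to 73% with 66. The figures for 66 assume that every randomised participant contributes full information; the planned carrying forward of last observations may change the effect itself.

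**What to change.** Keep the sample size, drop the word moderate, and restate section 2.8.1 for the planned four-visit group-by-time interaction. The restated paragraph should give:

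- the assumed correlation between visits;
- the difference detectable with 90% power, for an effect sustained over the post-baseline visits: about 0.92 SD with 46 analysed and about 0.77 SD with 66, at rho = 0.5;
- the power for a 0.5 SD sustained difference: about 37% with 46 and 52% with 66 at rho = 0.5, with the range over rho (27% and 39% at 0.3; 59% and 77% at 0.7);
- a sentence saying that a null result would not be evidence against a moderate benefit.

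The cost is one reworded paragraph. No participants are added, and the design and analysis do not change. The downside is that the stated power becomes less favourable.

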#### Statistical considerations

2.8.2

The analysis will adhere to the eHealth Consolidated Standards of Reporting Trials (CONSORT) criteria (Eysenbach, 2011), follow the intention-to-treat principle and per protocol set. The per-protocol set included participants who attended at least 70% of the assigned intervention sessions and completed all protocol-specified assessments (Zhang et al., 2018). Statistical analyses will be conducted using IBM SPSS Statistics (Version 24.0; IBM Corp., Armonk, NY, United States). Continuous variables are presented as mean and standard deviation; categorical variables as frequency and percentages.

For baseline characteristics, continuous variables are compared between groups using *t*-test, while categorical variables are analyzed using chi-square test. Primary outcomes will be analyzed using two-way repeated-measures ANOVA, evaluating the main effects of group, time, and their interaction. *Post-hoc* pairwise comparisons were conducted with Bonferroni correction for multiple comparisons. Missing follow-up data will be imputed using the last observation carried forward (LOCF) method. Sensitivity analyses (completers-only and per-protocol) will assess potential bias due to dropouts and imputation methods. We will also compare baseline characteristics between participants who dropped out and those who completed the study. All tests are two-sided, with statistical significance defined as *p* < 0.05.

Multimodal neurobiological correlates of treatment response will be assessed by integrating structural/functional MRI, gut microbiome, and plasma metabolome with behavioral outcomes. For analyses involving gut microbiota, key dietary patterns extracted from the 3-day food diaries will be included as covariates to enhance the validity of the findings. Hypothesis-driven analyses will include: (i) partial least squares (PLS) regression to identify multivariate brain-behavior associations, (ii) mixed-effects modeling for longitudinal effects, and (iii) mediation analysis to test whether brain-gut axis changes drive clinical improvement. Significance thresholds will be adjusted via Holm-Bonferroni correction.

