### Randomization and blinding

2.3

Participants will be randomly assigned in a 1:1 ratio to either the intervention group or the waitlist group using a computer-generated randomization sequence. To ensure baseline balance, randomization will be stratified by MCI subtype (amnestic vs. non-amnestic), baseline MoCA score (19–22 vs. 23–26), and age (60–65, 66–70, or 71–80 years). This approach ensures allocation concealment and minimizes selection bias. Due to the practical challenges of blinding participants, the study was conducted as a single-blind randomized controlled trial. Group allocation was concealed from partial research personnel—including outcome raters and data analysts—with the exception of the therapists administering the interventions, in order to reduce observer bias. All raters are explicitly prohibited from inquiring about participants’ group assignments, and all participants are instructed not to voluntarily disclose their treatment experiences or subjective impressions to raters.

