### Outcome measurements

2.5

The primary outcome is the change from baseline in a memory-weighted cognitive composite score, specifically designed to detect subtle changes over the trial period. This composite integrates tests that assess the cognitive domains most relevant to MCI, including: (1) Verbal learning and memory: total of five learning trials from the Chinese Auditory Verbal Learning Test (AVLT); (2) Delayed recall: 20-min delayed recall trial from the Chinese AVLT; (3) Executive function: Trail Making Test (TMT; Parts A and B); (4) Attention and working memory: Digit Span Test (DST; forward and backward).

To construct the composite score, raw scores from each test will be converted to Z-scores using the mean and standard deviation of the pooled sample at each test time point. For the Trail Making Test, where lower scores indicate better performance, Z-scores will be multiplied by −1 to ensure consistent directionality across all tests (higher Z-scores always indicate better performance). Based on the theoretical importance of memory function in MCI, the AVLT learning and delayed recall scores will receive a weight of 2, while the TMT and DST scores will receive a weight of 1. The final composite score will be calculated as the weighted average of these Z-scores (Andrade, 2021).

Secondary cognitive outcomes include changes from baseline in global cognitive function, assessed using the Montreal Cognitive Assessment (MoCA) and the Mini-Mental State Examination (MMSE). The MoCA provides a comprehensive assessment of multiple cognitive domains with high sensitivity for MCI (Nasreddine et al., 2005), while the MMSE is included to facilitate comparison with prior studies. Subjective cognitive decline will be assessed using the Alzheimer’s Disease 8-item scale (AD8), an informant-based measure that captures perceived changes in memory, orientation, and executive function.

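### The primary analysis tests group and group-by-time effects without saying which effect or visit decides the trial, and it leaves out the baseline composite and the stratification factors as covariates

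*Protocol article*

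**What the plan says.** The outcome is defined in section 2.5: "The primary outcome is the change from baseline in a memory-weighted cognitive composite score". No visit is attached to it, although post-baseline assessments fall at weeks 6, 12 and 24.

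The analysis is in section 2.8.2: "Primary outcomes will be analyzed using two-way repeated-measures ANOVA, evaluating the main effects of group, time, and their interaction". The threshold is common to all tests: "All tests are two-sided, with statistical significance defined as" p < 0.05. The only correction tied to the primary analysis concerns the follow-on comparisons: "pairwise comparisons were conducted with Bonferroni correction for multiple comparisons". Holm-Bonferroni appears only with the multimodal biomarker analyses.

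Section 2.8.1 reads: "Assuming a moderate effect size (f = 0.25), α = 0.05, and 90% power for a repeated-measures ANOVA", then "the minimum required sample size is 46 participants" and "To account for a 30% dropout rate, we will enroll 66 participants". It does not say which ANOVA effect was powered, for how many measurements, or at what correlation.

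Section 2.3 states that "randomization will be stratified by MCI subtype (amnestic vs. non-amnestic), baseline MoCA score (19–22 vs. 23–26), and age (60–65, 66–70, or 71–80 years"). That makes 2 × 2 × 3 = 12 cells. None of these factors, and no baseline covariate, appears in the stated primary model.

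**The concern.** A confirmatory claim needs one test whose error rate is controlled. Here two effects involve the randomised comparison, and the text lets either be read as the result. Which one carries the treatment effect depends on a point the article leaves open:

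- If raw composites at four visits are the response, the treatment effect sits in the interaction. The group main effect is diluted by a baseline visit at which no difference is expected.
- If changes at weeks 6, 12 and 24 are the response, the treatment effect sits in the group main effect. The interaction then asks only whether the benefit varies over time.

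The same sentence can therefore lead to different deciding tests, with different power. An interaction with several degrees of freedom is also significant for any difference in profile, so it does not by itself say that the intervention helped at a given visit. Section 3 reports that the primary outcome has already been changed from the registered MoCA, which is a further reason to close the success criterion now.

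Separately, the composite is measured at baseline and the randomisation is stratified. Using neither as a covariate gives up precision in a trial of 66 people.

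**Working it through.** **1. Reproducing the stated sample size.** Inputs from section 2.8.1: f = 0.25, α = 0.05, power 90%, 30% dropout. Assumed: two groups, correlation ρ = 0.5.

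- Interaction with m measurements: λ = N f² m/(1 − ρ), with df (m − 1) and (N − 2)(m − 1). For m = 2, N = 46: λ = 46 × 0.0625 × 2/0.5 = 11.5 and power is 91.2%. N = 44 gives 89.97%, so 46 is the minimum.
- Dropout: 46/0.7 = 65.7, rounded up to 66. Both stated figures reproduce.
- The time effect with m = 2 gives the same 46.
- The interaction at ρ = 0.5 needs 36 for m = 3 and 30 for m = 4. A four-visit interaction needs about 46 only at ρ between 0.2 (N = 48) and 0.25 (N = 44).
- Group main effect: λ = N f² m/(1 + (m − 1)ρ). It needs 130, 116 or 108 participants for m = 2, 3, 4. With N = 46 its power is 48–55%.

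**2. False positives.** For two independent tests at 0.05: 1 − 0.95² = 9.75%. Simulation under no effect (four visits, ρ 0.5 or 0.7, strata not prognostic) gives group or interaction significant in 9.7–10.2% of trials at N = 46, and about 9.8% at N = 66. If the strata explain an assumed 30% of variance and are left out of the model, the group test falls to 1.3–1.9%, the interaction stays near 5%, and either is significant in 6–7%.

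**3. Power by choice of test, N = 66.** Noncentral F, equal arms, unit SD, compound symmetry. With d the between-group difference and d̄ its mean over four visits:

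- group, raw scores: λ = (N/4) d̄²/[(1 + 3ρ)/4]
- interaction, raw scores, 3 df: λ = (N/4) Σ(d − d̄)²/(1 − ρ)
- group, change scores at three visits, d̄₃ the mean over those visits: λ = (N/4) d̄₃²/[4(1 − ρ)/3]
- week-12 change: λ = (N/4) d₁₂²/[2(1 − ρ)]
- week-12 ANCOVA: λ = (N/4) d₁₂²/(1 − ρ²)

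Example, first row below: d̄ = 0.3, so group λ = 16.5 × 0.09/0.625 = 2.38. ANCOVA λ = 16.5 × 0.36/0.75 = 7.92.

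| Assumed differences (SD), ρ | Group, raw | Interaction | Group, change | Week-12 change | Week-12 ANCOVA |
|---|---|---|---|---|---|
| 0, 0.3, 0.6, 0.3; 0.5 | 33% | 50% | 50% | 67% | 79% |
| same; 0.7 | 28% | 75% | 72% | 87% | 92% |
| 0, 0.25, 0.5, 0.5; 0.5 | 35% | 48% | 53% | 52% | 64% |
| same; 0.7 | 29% | 72% | 75% | 73% | 80% |

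Baseline adjustment against a change score gains 79 − 67 = 12, 92 − 87 = 5, 64 − 52 = 12 and 80 − 73 = 7 points.

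These effects are smaller than the one planned for. Setting the week-12 change λ equal to 11.5 at N = 46, ρ = 0.5 gives d₁₂ = 1.0 SD. The table therefore compares analyses; it does not re-estimate the trial's power.

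**4. Strata.** Simulated, N = 46, 0.5 SD at week 12, permuted blocks of 4 assumed, strata explaining an assumed 30% of variance. Adding them to the baseline-adjusted ANCOVA moves power from 48% to 53% (ρ 0.5) and from 64% to 65% (ρ 0.7). If they explain nothing, adding them costs 1–2 points.

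**The case against.** The best defence is that the deciding test can be inferred. The outcome is a change, the hypothesis is relative to the waitlist, and 46 fits an interaction. Part of this stands: the 10% arises only if either effect is accepted, and the article never says so. But 46 fits a time effect equally well, and it fits two measurements where the plan has four visits. The intended test therefore cannot be recovered from the text.

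Several stronger readings are tempting but unsupported:

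- *Three competing tests, about 14% error* (1 − 0.95³ = 14.3%). Time is not a treatment comparison. Section 2.5 also standardises each test on the pooled sample at every visit, which sets the pooled visit means to zero. In simulation the time effect was significant in 0.0% of trials.
- *Ignoring the strata inflates false positives.* It does the reverse for the group test and leaves the interaction at its nominal level.
- *Baseline is ignored.* The outcome is a change, so baseline enters by differencing or as a repeated level. What is missing is covariate adjustment.
- *The group effect is necessarily diluted.* This holds only for raw scores at four visits. With change scores its power is 50–75% in the table.

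An article may leave covariates to an analysis plan that is not shown, so the strata part is the weakest. It belongs here because the article does state its primary model, and a better one is nearly free. The first assumed profile also favours week 12 by peaking there. In the persisting profile at ρ = 0.7, the ANCOVA leads the interaction by only 80% to 72%.

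**Conclusion.** The concern holds in this limited form. No deciding effect or visit is fixed, and nothing controls error across the two treatment-related F-tests. Accepting either gives about 10% false positives, or 6–7% if the omitted strata are strongly prognostic. On raw four-visit scores the group effect has about 28–35% power at N = 66, and the stated sample size does not correspond to it. Omitting baseline and strata is a loss of power only: about 5–12 points and about 0–5 points respectively. The power figures rest on assumed effect profiles, correlations of 0.5 and 0.7, compound symmetry and complete data, none of which the article gives. The missing deciding contrast does not depend on them.

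**What to change.** Name one deciding contrast: the between-group difference in the composite at one pre-stated visit, tested at two-sided 0.05 and reported with a 95% CI. Week 12, the end of the intervention, is one reasonable choice. The investigators may prefer another visit, since section 3 justifies the composite by change over 24 weeks. Estimate the contrast from a mixed model or ANCOVA with the baseline composite, MCI subtype, MoCA band and age band as covariates. Label the group and time main effects and the other visits as supportive.

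State in section 2.8.1 that the calculation refers to this contrast, with the number of measurements and the correlation assumed. A two-measurement interaction with two groups is the same test as a comparison of change at one visit. The 46 therefore carries over if ρ = 0.5 is accepted.

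The cost is a few degrees of freedom (four for the strata, one for baseline), and the other visits leave the primary claim. No new data or visits are needed. The change should be made and dated before any unblinded look at the data.

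### LOCF is the primary handling of missing follow-up data with 30% dropout planned for, and neither named sensitivity analysis is a valid check if dropout depends on post-baseline scores

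*Protocol article*

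**What the plan says.** All of the following is in the protocol article.

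- **Primary analysis (2.8.2 Statistical considerations):** "Primary outcomes will be analyzed using two-way repeated-measures ANOVA, evaluating the main effects of group, time, and their interaction", under intention to treat.
- **Missing data (2.8.2):** "Missing follow-up data will be imputed using the last observation carried forward (LOCF) method".
- **Sensitivity analyses (2.8.2):** "Sensitivity analyses (completers-only and per-protocol) will assess potential bias due to dropouts and imputation methods". The per-protocol set consists of "participants who attended at least 70% of the assigned intervention sessions and completed all protocol-specified assessments".
- **Further check on dropout (2.8.2):** "We will also compare baseline characteristics between participants who dropped out and those who completed the study".
- **Planned dropout (2.8.1 Sample size):** "To account for a 30% dropout rate, we will enroll 66 participants".
- **Mixed models (2.8.2):** "mixed-effects modeling for longitudinal effects" is listed, but among the analyses of neurobiological data and not for the primary outcome.
- **Visits and arms (2.1 Study design):** assessments are at weeks 0, 6, 12 and 24. The waitlist arm is offered training only after the last assessment.
- **Composite (2.5 Outcome measurements):** each test is standardised at each visit against the pooled sample of that visit.

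The method for missing data and the sensitivity analyses are therefore stated choices, not details left to a fuller document.

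**The concern.** LOCF fills a missing visit with the participant's last score and then analyses it as if it had been measured. It is right on average only if nothing would have changed after that visit. Here change is expected in several ways: gains during 12 weeks of training, practice effects from four administrations of the same tests, and possible fading during 12 weeks without training. The sign of the error depends on the course of the scores. A growing benefit is diluted, because people who leave early keep their early scores. A fading benefit is overstated at week 24, because week-6 and week-12 scores stand in for later ones.

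The named sensitivity analyses are meant to catch such bias. Both are restricted to people with complete data, so neither uses anything observed in those who left. The estimates at stake are the group-by-time result for the primary outcome and the claim of maintenance at week 24.

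**Working it through.** **1. How many values are affected.** The enrolment figure reproduces: 46 / (1 − 0.30) = 65.7, rounded up to 66. At that dropout rate 66 × 0.70 = 46.2 participants reach week 24, so 66 − 46.2 = 19.8, about 20 final values, would be carried forward.

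**2. Expected LOCF estimate, dropout unrelated to outcome.** Formula: the expected LOCF effect at a visit is the sum, over last observed visits, of the probability of that last visit times the true effect at it.

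Assumptions (the document gives no trajectory or timing of dropout): 30% dropout in each arm, split evenly after weeks 0, 6 and 12, so the last-visit probabilities for weeks 0, 6, 12 and 24 are 0.1, 0.1, 0.1 and 0.7. The true effect is 0 at baseline, 0.25 SD at week 6 and 0.50 SD at week 12.

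- Effect sustained at 0.50, week 12: 0.1×0 + 0.1×0.25 + 0.8×0.50 = 0.425.
- Effect sustained at 0.50, week 24: 0.1×0 + 0.1×0.25 + 0.1×0.50 + 0.7×0.50 = 0.425. Against 0.50 this is 0.075 / 0.50 = 15% low.
- Effect fading to 0.10 at week 24: 0.1×0 + 0.1×0.25 + 0.1×0.50 + 0.7×0.10 = 0.145. Against 0.10 this is 0.045 / 0.10 = 45% high, or 0.045 SD in absolute terms.

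A large simulation with a constant dropout risk per interval (SD 1, correlation 0.6 assumed) gave 0.42 and 0.14 at week 24. Completers-only gave 0.50 and 0.10, the true values.

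**3. Unequal dropout with no true effect.** Assumptions: practice gains shared by both arms of 0.2, 0.4 and 0.5 SD at weeks 6, 12 and 24. Last-visit probabilities are 0.1, 0.05, 0.05, 0.8 in the arm with 20% dropout and 0.2, 0.1, 0.1, 0.6 in the arm with 40%.

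- Week 12: (0.05×0.2 + 0.85×0.4) − (0.1×0.2 + 0.7×0.4) = 0.35 − 0.30 = 0.05.
- Week 24: (0.05×0.2 + 0.05×0.4 + 0.8×0.5) − (0.1×0.2 + 0.1×0.4 + 0.6×0.5) = 0.43 − 0.36 = 0.07.

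This spurious difference favours whichever arm loses fewer people. It arises if raw scores are carried forward before standardisation. If the composite Z-score is carried forward instead, the shared gain has already been removed at each visit, and simulation gave 0.002 and −0.001. The errors in step 2 remain in that case (0.41 for 0.50, and 0.14 for 0.10). Section 2.8.2 does not say which is carried.

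**4. What the two sensitivity sets can show.** The per-protocol set requires all assessments, so it lies inside the completers. Its session rule (0.70 × 36 = 25.2, so at least 26 sessions) can act only on the intervention arm, since the waitlist has no sessions. Simulated week-24 differences when dropout depends on scores, same assumed SD and correlation:

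| Scenario | Truth | LOCF | Completers | MAR-based method |
|---|---|---|---|---|
| No effect; poor scorers at the previous visit leave the intervention arm (45% vs 15% dropout) | 0 | −0.13 | −0.06 | 0.00 |
| No effect; leaving the intervention arm depends on the unseen score (30% in each arm) | 0 | 0.04 | 0.04 | 0.10 |
| Effect 0.50; leaving the intervention arm depends on the unseen score (30% in each arm) | 0.50 | 0.46 | 0.54 | 0.60 |

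In the second row LOCF and completers agree while both are wrong, so agreement between the planned analyses would not be reassurance.

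**The case against.** A reader might infer that bias from dropout is never tested, or that the planned analyses cannot detect it. The document does not support that. When dropout is unrelated to outcome, as in steps 2 and 3, completers-only targets the right value and would tend to differ from LOCF, although its precision is limited in a trial of 66. The plan also compares baseline characteristics of dropouts and completers. What remains is narrower: neither check is valid when leaving depends on scores after baseline.

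A reader might also infer that LOCF will manufacture a benefit. Step 3 shows that this needs raw scores to be carried forward and, for shared practice gains, higher dropout in the waitlist arm. Nothing in the document points to that; a programme of 36 sessions could equally lose more intervention participants, which reverses the sign. With a sustained effect, LOCF is conservative.

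Nor are the controls in the per-protocol set unfiltered: the requirement of complete assessments applies to both arms. Only the session rule is one-sided, which is usual against a no-treatment control and is secondary to the intention-to-treat analysis.

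Finally, a MAR-based method is not always closer to the truth. In the last two rows of the table it is further off than LOCF. That objection stands, and it is why a mixed model alone is not enough.

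**Conclusion.** The point holds as a weakness in a stated method and should be fixed; the sizes shown do not make it a fatal defect. LOCF rests on an assumption that the design itself contradicts, and it would govern about 20 of 66 final values at the planned dropout. That 30% is a planning allowance, neither a ceiling nor a forecast. Under the illustrative assumptions the week-24 effect is 15% low if the benefit lasts and 45% high if it fades to 0.10 SD. The additional spurious difference of 0.05 to 0.07 SD applies only with unequal dropout and raw-score carry-forward.

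Dropout bias is not adequately tested: both sensitivity sets exclude all dropouts, and no MAR-based or MNAR analysis of the primary outcome is named. Trajectories, SD, correlation and dropout by arm are assumptions throughout. They show direction and possible size, not the bias this trial will have.

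**What to change.** - Analyse the primary outcome with a mixed model for repeated measures on all observed visits of all randomised participants, in place of LOCF with repeated-measures ANOVA.
- Add multiple imputation with delta adjustment, or with reference to the waitlist arm, as the sensitivity analysis, because the mixed model is itself biased when dropout depends on unseen scores.
- Keep the per-protocol analysis for the question of adherence if wanted, but do not present it as a check on dropout bias.
- If LOCF is kept as a supplementary analysis, state whether raw scores or the composite Z-score is carried forward.

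Cost: revised wording, modest extra programming, and possibly wider intervals. Mixed-effects modelling is already in the plan for the neurobiological data, and the sample size is unchanged.
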